**Figure 2 figure2:**
[figure not shown]
Protocol plan.

### Endpoints/Evaluation Criteria

#### Primary Outcome Measures

Change in respiratory symptoms (eg, dry cough, breath shortness, mouth irritation)

To evaluate the impact of a 3-month e-cigarettes program to reduce smoking-related respiratory symptoms (dry cough, breath shortness, mouth irritation, and phlegm) through reduced tobacco cigarette consumption. The primary outcome is measured at Month 6 and then at the follow-up at Month 12.

#### Secondary Outcome Measures

Change in psychological well-being (HAD scale)Change in number of cigarettes smoked dailyChange in the concentration of exhaled air COChange in daily activity (mean number of daily steps)Change in lifestyle as measured by ad-hoc questionnaires

### Statistical Considerations

#### Sample Size

Starting with data provided by previous studies on the effect of smoking discontinuation, whether using or not using e-cigarettes [2,20,21], we expected to find a reduction between 20% and 30% of respiratory symptoms reported by participants. We used cough as the measure to power the trial on. Using a two-sided *Z* test, a sample of 70 participants in either of the experimental groups (e-cigarettes with or without nicotine) and 70 in the control group (counseling alone) will reach 80% power, at .05 significance level, to detect a 20% reduction in the frequency of symptoms from the baseline in either of the e-cigarette groups (with or without nicotine) compared to a 5% reduction in the control group (counseling alone).

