
### Recruitment and Follow-Up

All inclusion and exclusion criteria are checked during the registration procedure and initial assessment for inclusion in COSMOS II. Eligible participants are asked to provide informed consent. The informed consent form is signed and dated by both the participant and the physician. Enrolled participants receive a chronological number and are assigned to a treatment group (e-cigarettes with nicotine, e-cigarettes without nicotine, or control).

A randomization list using a permuted block design (40 blocks of 6 subjects randomly assigned to 1 of the 3 treatment groups) have been previously prepared by an independent personnel unit and labeled with the progressive number applied to the packaging containing e-cigarettes and liquid cartridges with or without nicotine (Group 1 and Group 2).

Neither the participant nor the researcher in charge knows whether the liquid in the e-cigarettes kit contains nicotine. Only the statistician who prepared the randomization list and the person labeling the e-cigarettes packaging know the actual treatment.

Each participant is then assigned to one of the three groups and receives the related treatment, as illustrated above.

Follow-up: 6 months (at the IEO)

Behavioral psycho-cognitive questionnairesClinical parameters assessment (respiratory symptoms)Smoking status assessment (questionnaire and CO level). The nonsmoking status is established by self-report items and the CO level (ppm<5).Debriefing, during which we also ask participants of Group 1 and Group 2 to guess if they used a nicotine-free or a nicotine-based e-cigarette.

End-point: 12 months (at the IEO, during the annual assessment of COSMOS II)

Clinical parameter assessment (respiratory symptoms)Final behavioral and psycho-cognitive assessmentSmoking status assessment (questionnaire and CO level)Debriefing and collection of comments

Timeline (Figure 2):

Distribution of e-cigarettes: 3 months (ends at Week 12)Data tracking (e-bracelet) and active monitoring: 6 months (ends at Week 24)End point: 12 months

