### Statistical Plan

The main analysis will consist of comparing the reduction in symptoms after 6 months for the three groups: e-cigarettes with nicotine vs control; e-cigarettes without nicotine vs control; and e-cigarettes with nicotine versus e-cigarettes without nicotine. Analyses will be based on two-sided *Z* tests.

A secondary analysis will assess the reduction of the consumption of tobacco-containing cigarettes after 6 months among the groups. Analysis will be based on paired Student’s t-test or the Wilcoxon signed rank tests.

No interim monitoring is planned since, given the sample size, any interim analysis would have too few events to be interpreted. Efforts will be made to maximize retention by maximizing trust at the baseline assessment and collecting multiple means to contact and commit participants, including email and phone contact details, and by assertive follow-up. Starting with our previous experience with a similar population coming from the COSMOS I program, we expect that our participants will be compliant with and committed to the aims of the study. Giving the expected intrinsic motivation of participants and thanks to the above strategies, the study aims to have at least 80% retention at 6 months and 70% at 12 months. Considering these figures, we expect to maintain a statistical power to detect a reduction of 5 cigarettes/day in our smokers (the cigarettes per day mean is about 20 in the COSMOS population). Thus, using a two-sided two-sample *t*-test with a significance level (alpha) of .05, a sample size of 49 participants per arm will achieve 80% power to detect a mean reduction of 5 cigarettes/day between any of the 2 experimental arms and the control arm, assuming a mean consumption of 20 cigarettes/day in the control arm and a common standard deviation of 8.7.

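### The 80% power for the primary endpoint needs about 70 analysed per arm at Month 6, but at the plan's own minimum retention 56 or 64 remain, giving about 70% or 76%

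*Protocol article*

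**What the plan says.** Four statements in the protocol article bear on this point.

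- **Sample Size.** The trial is powered on cough with a two-sided Z test. The text says that "a sample of 70 participants in either of the experimental groups (e-cigarettes with or without nicotine) and 70 in the control group" "will reach 80% power, at .05 significance level", in order "to detect a 20% reduction in the frequency of symptoms from the baseline in either of the e-cigarette groups", "compared to a 5% reduction in the control group (counseling alone"). No allowance for dropout is mentioned.
- **Statistical Plan, analysis.** The main comparison of symptom reduction is made at 6 months, and "Analyses will be based on two-sided *Z* tests".
- **Statistical Plan, retention.** The authors write that "the study aims to have at least 80% retention at 6 months and 70% at 12 months". With these figures in mind they then turn to cigarettes per day, where "a sample size of 49 participants per arm will achieve 80% power" for a difference of 5 with a standard deviation of 8.7. They do not return to the primary endpoint.
- **Recruitment and Follow-Up.** "A randomization list using a permuted block design (40 blocks of 6 subjects randomly assigned to 1 of the 3 treatment groups") was prepared in advance.

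**The concern.** The primary power figure and the retention figure refer to the same time point, Month 6, yet the first is given as if nobody is lost. The only power statement that follows the retention figures concerns a secondary outcome. A reader can therefore come away believing that the trial's power has been shown to survive dropout, when this was shown only for cigarettes per day.

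The article also leaves open how 70 per arm relates to a list with room for 80 per arm. If 70 is the number to be enrolled, the primary analysis will have fewer than 70 per arm after any loss at all. If 70 is the number to be analysed and the list carries the margin, that margin has to be compared with the planned loss.

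What is at stake is how a null result on the primary endpoint is read. It would be judged against a type II error of 20%, when the plan's own minimum retention implies about 24% or 30%.

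**Working it through.** **Inputs.** From Sample Size: proportions .20 and .05, two-sided alpha .05, 70 per arm, stated power 80%. From Statistical Plan: analysis at 6 months; retention of at least 80% at 6 months and 70% at 12 months. From Recruitment and Follow-Up: 40 blocks of 6. Two assumptions are added: blocks are balanced 1:1:1, and the analysis uses participants with Month 6 data.

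**Step 1: reproduce the stated 80%.** Read 20% and 5% as the proportions of participants with a reduction. The pooled statistic is Z = (x1/n − x2/n) / √[2p̄(1 − p̄)/n], where p̄ is the mean of the two observed proportions. Exact power is the sum of Bin(x1; n, .20) × Bin(x2; n, .05) over all outcomes with |Z| ≥ 1.96. At n = 70 this gives 79.8%. The arcsine formula gives 80.4% and asks for 70 per arm. So the stated figure is reproduced, and it contains no reserve for attrition.

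A hand check uses the unpooled normal approximation, power = Φ(.15/SE − 1.96) with SE = √[(.20 × .80 + .05 × .95)/n] = √(.2075/n). At n = 70, SE = .0544 and power = Φ(.795) = 78.7%.

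**Step 2: numbers left at Month 6.**
- 70 enrolled per arm: 70 × .80 = 56.
- Full list: 40 × 6 = 240; 240/3 = 80 per arm; 80 × .80 = 64.
- Retention needed for 80 per arm to leave 70: 70/80 = 87.5%.
- Enrolment needed to leave 70 at 80% retention: 70/.80 = 87.5, so 88 per arm or 264 in all, which is more than the list holds.

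**Step 3: power for 20% against 5% at those numbers.**

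| Method | n = 70 | n = 64 | n = 56 |
|---|---|---|---|
| Exact, pooled Z | 79.8% | 75.9% | 70.2% |
| Exact, unpooled Z | 79.9% | 76.7% | 72.8% |
| Arcsine | 80.4% | 76.9% | 71.2% |
| Normal, unpooled | 78.7% | 75.0% | 69.3% |
| Normal, pooled | 77.1% | 73.3% | 67.4% |

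The range is 73–77% at 64 and 67–73% at 56. A continuity correction lowers every entry (68.4% at 70), but it does not reproduce the stated 80% and is not used here.

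**Step 4: difference detectable with 80% power (exact pooled Z, control 5%).** At 64 per arm, 21% gives 80.0%. At 56 per arm, 22% gives 78.6% and 23% gives 82.1%, so the detectable value lies between 22% and 23%.

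**Step 5: the secondary outcome.** A two-sample t-test for a difference of 5 with SD 8.7 needs 49 per arm and then has 80.4% power, as stated. It is also true that 70 × .70 = 49, but .70 is the 12-month retention, while the analysis of cigarette consumption is set at 6 months. At the 6-month numbers the same test has 85.4% power with 56 per arm and 89.7% with 64.

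**The case against.** The best case for the plan has four parts.

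- **Retention of 80% is a floor, not a forecast.** This stands. With 80 per arm, 85% retention leaves 68 (78.6% power) and 87.5% leaves the full 70. The figures of 70% and 76% hold only at the floor. But if 70 per arm is the number enrolled, any loss takes the analysis below 70.
- **The longer list may be the dropout margin.** It may be, though the article does not say so. Even then it covers a loss of 12.5% (10 of 80), not the 20% that the plan allows for.
- **The effect was set at the low end of the expected range.** Sample Size expects a reduction of 20% to 30% and powers on 20%. Against 5%, a true 25% would give 91.7% power at 64 per arm and 88.0% at 56. This limits the practical harm but does not make the stated 80% correct for 20% against 5%.
- **Missing participants could be kept in the analysis.** The article names no method. Counting them as unchanged gives 16% against 4% (each rate × .80), with power of about 70% at 70 per arm and 75% at 80, so the shortfall remains.

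Two stronger readings are tempting and are not supported. A reader might infer that 49 = 70 × 70% proves that 70 is the enrolled number. It suggests this, but the article never writes that product, and 49 is independently what the t-test requires. A reader might also infer that the plan has two conflicting enrolment targets, 210 and 240. Neither total is stated as a target, and a list may be longer than the number to be enrolled.

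**Conclusion.** The point holds as a gap between the primary power statement and the plan's own retention figure. The calculation at 70 per arm is not itself wrong. The stated 80% requires about 70 analysed per arm at Month 6. At the minimum planned retention the power is about 70% if 70 per arm are enrolled and about 76% if the list is filled, and every method in the table without a continuity correction stays below 80% in both cases. The shortfall is about 4 points in the better case and about 10 in the worse.

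This rests on reading 20% and 5% as proportions of participants (supported because it reproduces 70 per arm), on balanced blocks, on analysis of those with Month 6 data, and on retention at exactly 80%. It would disappear with 80 per arm enrolled and at least 87.5% retained. No adjustment for the three pairwise comparisons is included; one would lower the power further.

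**What to change.** Revise the sample-size text as follows.

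1. Say whether 70 per arm is the number enrolled or the number evaluable at Month 6, and how it relates to the 240-place list.
2. Give the expected evaluable number per arm at Month 6.
3. Restate the primary power at the planned 80% retention: about 76% with 64 per arm, or about 70% with 56. Alternatively, give the difference detectable with 80% power: about 21% against 5% with 64 per arm, or about 22–23% against 5% with 56.
4. For both the primary and the cigarettes/day outcome, use the retention figure that belongs to the time of analysis, which is 6 months.

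The cost is a few sentences. No participants are added and no endpoint, test or error rate changes. The stated primary power becomes less favourable.

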### Participants

Volunteer smokers are recruited from among COSMOS II participants at the IEO hospital. Details on the inclusion and exclusion criteria are provided in the “Selection Criteria” section below.

The main inclusion criterion is adult healthy smokers who voluntarily choose to take part in a lung cancer screening program. This screening program includes both a low-dose computed tomography (CT) scan and blood tests in order to detect early signs of lung cancer. Consequently, all of our participants agree to undergo these examinations and are over the age of 55 at the beginning of the study. To be included in the study, COSMOS II participants must have smoked an average of 10 cigarettes or more a day for at least the past 10 years. Furthermore, they also must report strong motivation to stop smoking as measured by a motivational questionnaire (see the “Instruments and Measures” section).

Since we are interested in assessing the effect of a specific e-cigarettes-based treatment, we exclude smokers already using e-cigarettes, which we define as smokers who had ever regularly used e-cigarettes for more than 1 week alone or in combination with tobacco cigarettes. Thus, all participants are inexperienced with the use of e-cigarettes (full instructions are provided by the researcher in charge of the study during the briefing). Also, smokers who at the moment of the interview are undergoing NRT or underwent NRT in the previous 6 months are excluded. In this way, we tried to prevent any psychological and physiological confounding effects due to previous treatments. Furthermore, people with a history of psychiatric, severe dyspnea, and cardiovascular diseases are also excluded.

All the including and excluding criteria are evaluated during the first clinical examination of the COSMOS II program. Only after the clinical examination, which includes objective tests and an anamnestic interview by a physician in charge, is a smoker considered for possible inclusion in the protocol.

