#### Instruments

Self-reported measures are used for cough and other respiratory symptoms assessment. We opted for Likert scales to measure cough, breath shortness, mouth irritation, and phlegm frequency as well as the Leicester Cough Questionnaire.Fagerstrom Test for Nicotine Dependence: a 6-item self-reporting questionnaire assessing nicotine dependence. It requires a few minutes to complete [12]. This test is administered to all COSMOS II participants.Motivational questionnaire [13]: a 4-item self-reporting questionnaire assessing motivation to quit smoking. The total classifies the patient into 1 of 4 motivational categories (from “not ready to quit” to “highly motivated”). This test is administered to all COSMOS II participants.Hospital Anxiety and Depression Scale (HAD): The HAD is a self-administered questionnaire composed of two 7-item scales, 1 for anxiety and 1 for depression, which should be used as 2 separate measures of emotional distress. The scale has been validated for Italian culture by Costantini and showed high internal consistency with Crohnbach alpha, ranging from .83 to .85 [14]. The HAD evaluates symptoms of anxiety and depression, avoiding misattribution due to the physical aspects of the illness. The values range from 0 to 21 for each scale. Cutoff scores are preliminarily defined as normal (0-5), mild (6-8), moderate (9-11), and severe (greater than 11) for both anxiety and depression patients [15].BIS/BAS Scale [16]: a 20-item self-reporting questionnaire evaluating the behavioral inhibition system (BIS) and BAS. Each of the items is rated on a 5-point scale, ranging from 1 (does not describe me at all) to 5 (describes me very well).Barratt Scale [17]: an 11-item self-reporting questionnaire designed to measure impulsiveness. All items are measured on a 4-point scale (Rarely/Never; Occasionally; Often; Almost Always/Always), where a 4 generally indicates the most impulsive response, although some items are scored in reverse order to avoid a response bias [18].The Leicester Cough Questionnaire: a valid, self-reported cough-specific health status measure. It is a 19-item questionnaire that has been validated in acute and chronic cough [19]. The overall score ranges from 3 to 21 with a higher score indicating a better quality of life.Electronic bracelet (the Flex FitBit): a device that allows lifestyle monitoring of physical activity and sleep characteristics, including: sleeping and napping (hours slept, light vs deep sleep, and waking periods); activity (distance, calories burned, activity time, and activity intensity); nutrition (food and beverage intake); mood (assessment of the affect state); and an insight engine that identifies hidden connections and patterns in day-to-day activities.The exhaled CO is measured by the The Micro+ Smokerlyzer, which has less than 5% H_2_ cross-sensitivity.Ad hoc questionnaire: measures demographic data, self-perceived quality of life (analogue scale), physical activity, and smoking-related issues (characteristics of the smoking experience).

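### The stated 80% power fits two simple proportions (20% vs 5%), but the primary comparison is of change from baseline in graded symptom scores; the power needs restating and the comparison adjusting for baseline cough

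*Protocol article*

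**What the plan says.** All references are to the protocol article.

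- **Sample Size.** Cough is the variable on which the trial is powered. The plan takes "a sample of 70 participants in either of the experimental groups" and 70 controls, says this "will reach 80% power, at .05 significance level", and gives the effect as enough "to detect a 20% reduction in the frequency of symptoms from the baseline in either of the e-cigarette groups", set against a 5% reduction with counseling alone. The test is a two-sided Z test. No SD, baseline prevalence or definition of an improved participant accompanies the figures.
- **Primary Outcome Measures.** The outcome is change in respiratory symptoms, measured at Month 6 and again at Month 12.
- **Instruments.** "We opted for Likert scales to measure cough, breath shortness, mouth irritation, and phlegm frequency as well as the Leicester Cough Questionnaire". The Leicester total runs from 3 to 21.
- **Statistical Plan.** "The main analysis will consist of comparing the reduction in symptoms after 6 months for the three groups", pair by pair. "Analyses will be based on two-sided *Z* tests". No covariate is named. For cigarettes per day, by contrast, the same section gives a mean, an SD of 8.7 and a two-sample t-test.

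**The concern.** A power statement is useful only if its inputs describe the variable that will be tested. Here the wording describes a percentage reduction from baseline, the instruments produce graded scores, and the arithmetic turns out to be that of two proportions. A percentage reduction could mean the share of people who improve, the fall in the share who have cough, or the fall in the mean score. These are three different endpoints, and 70 per arm has a different power for each. A reader who takes the 80% at face value may be relying on a figure that does not belong to the comparison to be made.

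There is a second, smaller matter. The trial must record baseline cough in order to compute a reduction, yet the named primary test makes no adjustment for it. A chance difference between arms in baseline cough then feeds into the comparison of reductions, because high scores tend to fall and low scores tend to rise. Precision that costs nothing to obtain is left unused.

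**Working it through.** **Inputs from the article:** two-sided alpha 0.05, power 80%, 70 per arm, effects 20% and 5%. **Inputs it does not give, assumed below:** baseline prevalence of cough, SD of the change, and baseline-to-follow-up correlation r. Every power figure in steps 1 to 4 takes 70 analysed per arm and leaves dropout aside. Constants: 1.960 + 0.842 = 2.802.

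**1. Reproducing the plan's figure, as two proportions.**
- Arcsine formula: h = 2·asin(√0.20) − 2·asin(√0.05) = 0.927 − 0.451 = 0.476. Then n = 2 × 2.802² / 0.476² = 69.2, so 70 per arm. Power at 70 is Φ(0.476 × √35 − 1.960) = Φ(0.858) = 80.4%.
- Exact binomial power of the Z test at 70 per arm: 79.8% with pooled variance, 79.9% unpooled.
- The usual approximations come close: pooled n = 76 (77.1% power at 70), unpooled n = 73 (78.7%).

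So 70 per arm and 80% are right for independent proportions of 20% and 5%. They cannot be derived as a comparison of mean changes, because no SD is given.

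**2. Read as a change in mean score.** The difference between arms is 20% − 5% = 15% of the baseline mean. With s the SD of change as a fraction of that mean, power = Φ(0.15 / (s·√(2/70)) − 1.960).

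| s (assumed) | Power at 70 per arm | n per arm for 80% |
|---|---|---|
| 0.3 | 0.841 | 63 |
| 0.4 | 0.602 | 112 |
| 0.5 | 0.427 | 175 |
| 0.6 | 0.315 (0.312 with the t distribution) | 252 |

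Break-even: the standardised difference needed is 2.802 × √(2/70) = 0.474, so s = 0.15 / 0.474 = 0.32.

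**3. Read as a relative fall in the prevalence of cough**, comparing Month-6 prevalences with the pooled formula.
- Baseline 50% (assumed): 0.50 × 0.80 = 40% vs 0.50 × 0.95 = 47.5%. Null SE = √(2 × 0.4375 × 0.5625 / 70) = 0.0839; alternative SE = 0.0836. Power = Φ((0.075 − 1.960 × 0.0839) / 0.0836) = Φ(−1.07) = 14%.
- Baseline 70% (assumed): 56% vs 66.5%. The same steps give Φ(−0.69) = 25%.

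**4. What adjustment for baseline is worth if the score is analysed.** With equal variance σ² at both visits, the variance per participant is 2σ²(1 − r) for a change score and σ²(1 − r²) for ANCOVA. The ratio is (1 + r)/2: 0.65 at r = 0.3, 0.75 at r = 0.5, 0.85 at r = 0.7.

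Illustration, with raw SD 0.5 of the mean and r = 0.5, both assumed: the SD of change is 0.5 × √(2 × 0.5) = 0.50, giving power 43%. The ANCOVA residual SD is 0.5 × √0.75 = 0.433, giving power 54%.

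**The case against.** The best defence is that the plan is coherent on one reading. If 20% and 5% are the shares of participants who improve, the sizing test and the planned test are the same Z test and the 80% is correct before dropout. The remark in the Statistical Plan that an interim look would have too few events fits such a yes/no endpoint. A condensed article may also leave the responder rule, the choice of score and the covariates to a fuller document. Most of this stands. The absence of those details is not the point here. What remains is that the article itself prints a power figure and a primary test, and describes the effect and the outcome in terms that do not identify the endpoint the figure belongs to.

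Several stronger readings are tempting, and the article does not support them.

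- *That baseline is discarded.* The comparison is of reductions, so baseline enters through the change. Only covariate adjustment is missing, and the unadjusted randomised comparison remains valid.
- *That a Z test forces a yes/no split.* A Z test can compare mean changes. The article never says that it dichotomises; the proportions are inferred from the arithmetic.
- *That the trial is underpowered.* Steps 2 and 3 rest on assumed inputs, and a mean-change analysis keeps 80% when the SD of change is at most about 0.32 of the baseline mean.
- *That participants without cough dilute the effect.* The article does say "The main inclusion criterion is adult healthy smokers who voluntarily choose to take part in a lung cancer screening program" and sets no cough criterion. But 20% and 5% may already be shares of everyone, and only severe symptomatic respiratory disease is excluded.
- *That a score endpoint is necessarily better.* If benefit is confined to the 20% and 5% who improve, by an assumed 1 to 3 SD, simulated ANCOVA power at 56 per arm is 0.16 to 0.62, against about 0.70 for a responder Z test.

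**Conclusion.** The point holds in a limited form. The stated 70 per arm and 80% power are arithmetically sound for two independent proportions of 20% and 5%, and they transfer to the primary comparison only if those are the shares of all randomised participants who improve. On the other readings the wording allows, power at 70 per arm differs: 84% to about 31% for a mean change (SD of change 0.3 to 0.6 of the baseline mean), and about 14% or 25% for a relative fall in prevalence from 50% or 70%. These ranges show how much depends on the missing definition. They are not estimates of the trial's true power.

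Separately, the named primary test is unadjusted although baseline cough has to be available. For a score analysis, adjustment reduces the variance to 0.65 to 0.85 of the change-score value for r between 0.3 and 0.7, assuming equal variances at the two visits. Whether the endpoint should be a score or a responder share is a design choice on which this point takes no position.

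**What to change.** 1. State in Sample Size what 20% and 5% are percentages of, and name the cough variable that the Month-6 primary comparison uses.
2. Restate the power for that variable with matching inputs: the two proportions and the rule for improvement if it is a responder endpoint; the mean difference and SD of change (or residual SD) if it is a score; the baseline prevalence if it is presence or absence of cough.
3. Adjust the Month-6 primary comparison for baseline cough: ANCOVA if the score is analysed, or a baseline-adjusted comparison of proportions if a responder endpoint is intended.

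The cost is a rewritten power paragraph and one line in the Statistical Plan. No new data are needed, since baseline cough is already required to compute a reduction. If the restated calculation shows less than 80% power at 70 per arm, the sponsor should report that openly. The article gives the trial's status as recruiting at submission, so the wording should be settled before any unblinded outcome data are seen.
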